### Intervention

The Wintersportklaar intervention has been developed according to the steps of Intervention Mapping (IM) and Knowledge Transfer Scheme [8-10]. The Fogg Behaviour Model (FBM) to achieve behavior change formed the basis for this development [11]. More information on the development of Wintersportklaar is available in [name], [name] & [name] (under review).

Wintersportklaar will be made available exclusively to the participants within the intervention group, and is an evidence-based intervention developed to stimulate injury preventive behavior among skiers and snowboarders. The development of the intervention was a collaboration between snow sport experts and the target group. According to the Dutch winter sport experts who were consulted, the skill level and the physical fitness level of skiers and snowboarders are the two main dimensions involved in the risk of winter sport injuries.

**Figure 1 figure1:**
[figure not shown]
Flowchart of participants of the randomized prospective controlled trial.

Part one of the intervention is a short questionnaire. Based on 8 single questions, the physical fitness and skill level of the skiers and snowboarders will be determined and classified as: 1) low level of physical fitness and skill level; 2) low level of physical fitness and sufficient skill level; 3) sufficient level of physical fitness and low skill level; and 4) sufficient level of physical fitness and skill level. Depending on their answers, skiers and snowboarders will receive tailored advice on optimal preparation for their winter sport holiday (part two). Examples of advice include taking winter sport lessons, and strength exercises. Furthermore, advice about the use of protective gear and the 10 Fédération Internationale de Ski (FIS) rules for the conduct of winter sport safety are given. After receiving the tailored advice, the skiers and snowboarders can leave their email address on the website in order to receive a personal exercise schedule every week until the start of their winter sport holiday (part three). The Wintersportklaar intervention is made available to the participants within the intervention group. Huge efforts have been made to develop an easily accessible intervention (eg, short questionnaire, quick outcome), with a low threshold, and easily applicable injury preventive advice.

### The Control Group

The skiers and snowboarders in the control group do not have access to the intervention and prepare their winter sport holiday as they normally would.

### Injury Preventive Behavior

In our study, our main outcomes measure injury preventive behavior defined as: (i) taking winter sport lessons; (ii) performing strength exercises; (iii) the use of protective equipment; and (iv) knowledge of the 10 FIS rules for the conduct of safety in winter sport. Each injury preventive topic is divided into preparatory acts like searching for information about injury preventive measures, buying a winter sport helmet, etc, and structural injury preventive measures (eg, wearing a helmet, taking lessons). Taking winter sport lessons consists of two preparatory acts and three structural injury preventive measures. Performing strength exercises consists of two structural injury preventive measures, and the use of protective gear consists of three preparatory acts and three structural injury preventive measures. Finally, knowledge of the 10 FIS rules for the conduct of safety in winter sport consists of three preparatory acts. All injury preventive behaviors are assessed through single questions (eg, Did you buy a winter sport helmet after the start of this study? Yes/No/Not applicable).

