### Objective and Hypothesis

The objective of the study is to evaluate the effectiveness of the Wintersportklaar intervention (www.wintersportklaar.nl; in Dutch) on injury preventive behavior among skiers and snowboarders. The hypothesis of this study is that the developed intervention would lead to a 10% increase in favorable injury preventive behavior in the intervention group in comparison to the control group.

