### Study Design

A randomized controlled trial with a follow-up period of 4 months during the winter sport season will be conducted (see Figure 1). The study is registered in the Dutch Trial Registry (ID: NTR6233).

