### Procedures

At baseline, respondents will be asked about their winter sport demographic characteristics, winter sport skill level, physical fitness, current injuries and physical complaints, winter sport preparation, and winter sport injury preventive measures. Furthermore, skiers and snowboarders in the intervention and control group will be asked to report the injury preventive measures they usually take during their preparation for their winter sport holiday. One month and three months after baseline, skiers and snowboarders will be asked to report retrospectively in detail what they had done up until then regarding injury prevention during their current winter sport preparation and holiday. In the follow-up measurements, respondents will be asked about any injuries they suffered during their winter sport preparation and holidays. In our study, an injury is defined as an event during skiing or snowboarding after which the participants have to stop their winter sport activities or are unable to participate in another winter sport activity [12-15]).

For all three measurements, an online form will be sent by email by 1 researcher through SurveyMonkey, an online questionnaire system (www.surveymonkey.nl). The first reminder will be sent after 1 week if no response is received. A second reminder will be sent after 2 weeks if no response is received.

The intervention group will be additionally questioned about their use and valuation of the Wintersportklaar intervention. The evaluation of its effectiveness will not take place in an experimental setting; participants in the intervention group will be given access to the intervention, but no further conditions are applied to the use of the intervention. In the questionnaires given at one month and three months, the intervention group will be asked about their use of the intervention, the appeal of the intervention, the behavioral actions they took after being exposed to the intervention, their intention to use the intervention again, and how they would want to be informed about the intervention. If participants indicate that they do not want to use the intervention, they will be asked to explain their decision in detail.

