### Statistical Analysis

Descriptive analyses (mean, standard deviation, frequency, range) are conducted for the different baseline variables for both study groups. To evaluate the success of the randomization, baseline values are analyzed for differences between the intervention and control groups (chi square, independent *T* tests and/or Mann-Whitney test).

Chi square tests and/or logistic regression analyses will be used to analyze behavioral change according to the intention to treat principle. According to this principle all participants who were enrolled and randomly allocated to the intervention or control group are included in the analysis and are analyzed in the groups to which they were randomized. In a secondary analysis, behavioral change is analyzed according to the non-intention to treat principle. The proportion of injured winter sport participants is calculated by dividing the number of injured respondents by the total number of respondents in this study and per study group. Differences in the proportion of winter sport injury between the intervention and control groups are assessed using logistic regression analysis (significance level set at *p*<.05).

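### Hypothesis and sample size rest on one comparison, but four main outcomes (16 questions, two follow-ups) are defined and none is fixed as primary

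*Protocol article*

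**What the plan says.** **One quantity.** The Protocol article, Objective and Hypothesis, expects that "the developed intervention would lead to a 10% increase in favorable injury preventive behavior in the intervention group in comparison to the control group". Sample Size and Allocation turns this into 423 per group, with a significance level of 0.05, 80% power and 10% loss to follow-up. The Discussion treats injury preventive behavior as a primary outcome measure and sets 10% as the relevant change.

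**Several quantities.** The Injury Preventive Behavior section says "our main outcomes measure injury preventive behavior defined as: (i) taking winter sport lessons; (ii) performing strength exercises", followed by protective equipment and knowledge of the ten FIS rules. Each topic is split into items. For the first topic: "Taking winter sport lessons consists of two preparatory acts and three structural injury preventive measures". For the others, the section counts two structural items under strength exercises, three items of each kind under protective gear, and three items under the FIS rules, all of them preparatory. On measurement: "All injury preventive behaviors are assessed through single questions", with an example that offers Yes, No and Not applicable.

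**Timing and analysis.** Procedures: "One month and three months after baseline, skiers and snowboarders will be asked to report retrospectively" on what they have done so far. Study Design: "A randomized controlled trial with a follow-up period of 4 months during the winter sport season will be conducted". Statistical Analysis: "Chi square tests and/or logistic regression analyses will be used to analyze behavioral change according to the intention to treat principle". That section does not say which outcome or which follow-up is tested. Its p<.05 is attached to the comparison of injury proportions.

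**The concern.** A 10% increase can be confirmed or refuted only if the reader knows which proportion is meant to rise, and when. The article names four candidates at topic level and 16 at item level, at two follow-ups, and does not choose or combine them. The stated 0.05 and 80% power belong to a single test that the plan does not identify. The choice could then be made after the results are known, and a favorable result on one topic or question could be presented as the trial's answer. The choice of follow-up also changes what is measured. The one-month form asks about behavior up to that date, so measures taken on the slopes, such as wearing a helmet, cannot yet have occurred in anyone who has not travelled.

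**Working it through.** **Step 1. Count the outcomes** (Injury Preventive Behavior).

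| Topic | Preparatory | Structural | Total |
|---|---|---|---|
| Lessons | 2 | 3 | 5 |
| Strength exercises | 0 | 2 | 2 |
| Protective gear | 3 | 3 | 6 |
| FIS rules | 3 | 0 | 3 |
| All | 8 | 8 | 16 |

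With two follow-ups (Procedures) there are up to 4 × 2 = 8 topic-level or 16 × 2 = 32 item-level comparisons.

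**Step 2. What the 423 fits.** No control rate is given, so 423 cannot be reproduced from the stated inputs alone. I read the 10% as absolute and the test as two-sided, and use

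n = [z(1−α/2)·√(2p̄(1−p̄)) + z(0.80)·√(p₁(1−p₁) + p₂(1−p₂))]² / (p₂−p₁)², divided by 0.9 for loss.

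- Assumed 40% vs 50%: n = 388, and 388/0.9 gives 432.
- 423 is met exactly at assumed control rates of about 36% or 54%, and within 3% at 34–43% or 47–56%.
- Read as a 10% relative increase, a control rate near 78% is needed (382, inflated to 425).

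So 423 is consistent with one comparison of one proportion at the stated 0.05. The arithmetic alone does not exclude a split level: α = 0.05/4 at an assumed control rate of 17% gives 382, inflated to 425. But the article states 0.05 and mentions no split.

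**Step 3. Familywise error if outcomes are tested separately at an unadjusted 0.05.** For k independent tests it is 1 − 0.95^k. For correlated tests it was simulated with equicorrelated normal test statistics; the correlations are assumptions.

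| Tests | Independent | 0.1 | 0.3 | 0.5 | 0.9 |
|---|---|---|---|---|---|
| 4 (topics, one follow-up) | 18.5% | 18% | 17% | 16% | 9% |
| 16 (items, one follow-up) | 56.0% | 55% | 47% | 37% | 15% |
| 32 (items, both follow-ups) | 80.6% | 79% | 68% | 52% | 18% |

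Eight independent topic tests (both follow-ups) give 33.7%.

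**Step 4. Power if 0.05 is split.** Completers per arm: 423 × 0.9 = 380.7, so 381. For an assumed 50% vs 60%,

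Power = Φ{[0.10 − z(1−α/2)·√(2 × 0.55 × 0.45/381)] / √((0.50 × 0.50 + 0.60 × 0.40)/381)}.

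- α = 0.05: (0.10 − 1.960 × 0.03604)/0.03586 = 0.82, power 79%.
- α = 0.05/4: (0.10 − 2.498 × 0.03604)/0.03586 = 0.28, power 61%.

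Over assumed control rates from 10% to 50%, always with a 10-point gain, power runs from 97% down to 79% at 0.05, and from 92% down to 61% at 0.05/4. At 40% or 50% control, 80% power at 0.05/4 needs 551 completers per group, inflated to 613.

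**The case against.** The strongest reply is that this is a condensed article. A scoring rule, a multiplicity procedure or a named endpoint may stand in a full protocol or analysis plan that is not shown. For the multiplicity procedure this is right, and its absence here is not the point. It does not remove the mismatch: the article describes its outcomes down to the number of questions per topic, defines four of them, and powers the trial as if there were one.

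Three stronger readings are tempting, but the article does not support them.

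- **That every item is tested at 0.05.** A reader might infer this from the chi-square or logistic tests and the single questions. No passage says it. For behavior, 0.05 appears only in the sample size.
- **That a false positive is likely.** The main outcomes stand at topic level, where four tests at one follow-up give about 9–19%. The risk exceeds one half only if many items are tested separately with weak to moderate correlation. Independence of all 32 is implausible, because the three-month form asks about everything done so far and so largely contains the one-month answers.
- **That a four-month follow-up with a last questionnaire at three months is a plain contradiction.** Reminders after one and two weeks carry data collection past three months, and the flow chart is not shown. The two statements need reconciling, but the point is minor.

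**Conclusion.** The concern holds in this form: the hypothesis and the 423 per group assume one comparison, while four main outcomes with 16 questions at two follow-ups are defined and none is fixed as primary. This follows from the text and needs no assumption.

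Its size is conditional. With separate unadjusted tests at 0.05, familywise error is about 19% for four independent topic tests, nearly four times the stated level. It is 56% for 16 independent tests and 81% for 32, and lower with correlation. If 0.05 is divided over four topics, power per topic falls from 79% to 61% under the assumed 50% vs 60% with 381 completers per arm, and falls less where the control rate is further from one half. These figures assume a 10-point absolute gain and two-sided tests, neither of which the article states.

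**What to change.** **Preferred.** Name one primary endpoint at the three-month questionnaire that covers all four topics, for example the proportion of applicable items answered yes. Leave Not applicable answers out of the denominator and report their number by arm. Estimate one treatment effect in one model across items with participant-clustered standard errors. Test the four topics as secondary outcomes with Holm, and report single items and one-month data with confidence intervals only. Do not restrict the endpoint to structural measures: the FIS-rules topic has none, so it would drop out together with all 8 preparatory items. State the weighting as well, since an unweighted proportion gives protective gear 6 of 16 items and strength exercises 2 of 16.

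**Alternative.** Keep the four topics as co-main outcomes at three months, define a score for each, test them with Holm and restate the power.

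**In either case.** State whether the 10% is absolute or relative and to which endpoint it applies. Reconcile the four-month follow-up with the last questionnaire at three months. Since the Results section says that analysis is under way, record the choice with a date before arm-level results are examined. If they have been seen, disclose the choice as post hoc.

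**Cost.** Wording only, with no new data. Under the preferred option single-item results can no longer be headline claims, and one common effect can mask differences between topics. The alternative lowers the power per topic. If results have already been seen, wording cannot restore a prespecified endpoint.

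### The main outcomes mix information-seeking with preventive behavior, and the FIS-rules outcome labelled knowledge contains no measure of knowledge

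*Protocol article*

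**What the plan says.** Under Methods, Injury Preventive Behavior, the article states that "our main outcomes measure injury preventive behavior defined as: (i) taking winter sport lessons; (ii) performing strength exercises", followed by use of protective equipment and knowledge of the 10 FIS rules. It says that each topic is divided into preparatory acts and structural measures. The first kind is described as "preparatory acts like searching for information about injury preventive measures, buying a winter sport helmet, etc"; wearing a helmet and taking lessons are the examples of the second.

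The item counts are given topic by topic: "Taking winter sport lessons consists of two preparatory acts and three structural injury preventive measures"; "Performing strength exercises consists of two structural injury preventive measures"; "the use of protective gear consists of three preparatory acts and three structural injury preventive measures"; and "Finally, knowledge of the 10 FIS rules for the conduct of safety in winter sport consists of three preparatory acts". Answers are yes, no or not applicable.

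Under Intervention, the website gives tailored advice on lessons and strength exercises, and advice on protective gear and the FIS "rules for the conduct of winter sport safety are given". Under The Control Group: "The skiers and snowboarders in the control group do not have access to the intervention". The Statistical Analysis section tests behavioral change without distinguishing the two item types.

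**The concern.** Two separate problems follow from these definitions.

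First, a label does not match its measure. An outcome named knowledge should contain something that a person with the knowledge would answer differently from a person without it. Three preparatory acts do not do that. A difference between groups on this topic would show that more people took those steps, and nothing about what they know.

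Second, exposure and outcome overlap. Searching for information is a named preparatory act, and the intervention is itself an information source on the same topics, open to one group only. A participant who used the site may answer yes to an information item for that reason alone. Controls can still answer yes by searching elsewhere, but not by this route. If such items carried a positive result, the report could claim a change in injury preventive behavior when it had shown only that the intervention was delivered.

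**Working it through.** **Item count, from Injury Preventive Behavior.**

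| Topic | Preparatory | Structural |
|---|---|---|
| Lessons | 2 | 3 |
| Strength exercises | 0 | 2 |
| Protective gear | 3 | 3 |
| FIS rules | 3 | 0 |
| Total | 8 | 8 |

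The preparatory share is 8/16 = 50% overall: 2/5 for lessons, 0/2 for strength exercises, 3/6 for protective gear and 3/3 for the FIS rules. The statement that every topic is divided into both kinds fails for two of the four: strength exercises has structural items only and the FIS rules preparatory items only.

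**The target difference.** The article gives 10%, 80% power, a significance level of 0.05, 10% loss and 423 per group, but no control rate. One set of inputs that reproduces 423 is a two-sided test with unpooled variance, 40% against 50% (or 50% against 60%): 7.849 × 0.49 / 0.01 = 384.6, and 384.6 × 1.10 = 423.1. This is compatible with reading the 10% as 10 percentage points. That reading is used below and is an assumption.

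**What exposure alone could do to one information item.** Let *b* be the control rate of yes. Let *u* be the share of the intervention group that uses the site and answers yes because of it. Assume that users would otherwise have had the same rate *b* and that nothing else changes. Then

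difference = *u*(1 − *b*), which equals 0.10 when *u* = 0.10/(1 − *b*).

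| *b* (assumed) | *u* needed for 10 points |
|---|---|
| 30% | 0.10/0.70 = 14% |
| 50% | 0.10/0.50 = 20% |
| 70% | 0.10/0.30 = 33% |

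With 423 × 0.90 ≈ 381 analyzed per group, *b* = 50% and *u* = 20%, the comparison is 50% against 60%. The standard error under the null is √(2 × 0.55 × 0.45/381) = 0.0360, so the critical difference is 1.96 × 0.0360 = 0.0706. The standard error under the alternative is √((0.25 + 0.24)/381) = 0.0359. Then (0.10 − 0.0706)/0.0359 ≈ 0.82, a 79% chance of significance on that one item.

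**What it could do to a combined score.** The article does not say how items are combined. If the 16 were averaged with equal weight (an assumption), a 10-point exposure effect on one item would move the average by 10/16 = 0.6 points, and on three items by 30/16 = 1.9 points. The overlap is therefore serious for single items and for the FIS topic, and small for an overall average unless many items are affected.

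**The case against.** A reader might infer that the whole preparatory half of the main outcome is met simply by opening the website. The article does not support that. Its own description of preparatory acts also names buying a helmet, which is real behavior that a site visit does not satisfy, and the one item whose wording is printed is about that purchase. The other preparatory items are not listed, so the number that concern information is unknown. It is also an inference that respondents would count a study-supplied site as their own search; the questionnaire may exclude it, and a condensed article would not normally print every item. All of this stands, and it limits the second problem to an unknown number of information-seeking items.

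The arithmetic has limits too. It concerns one item, both *u* and *b* are assumed, and site users may be people who would have searched anyway. If users' own rate were 70% when controls' was 50%, the gain from exposure would be 0.30*u* instead of 0.50*u*, and 33% rather than 20% would be needed.

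Finally, including preparatory acts is a reasoned choice. The intervention rests on a behavior-change model, and the Discussion argues that change comes in small steps and that the split improves measurement. That is a fair defense of collecting these items, and a reason not to insist that only structural items be primary. It does not answer the FIS label, and it gives no reason to pool the two kinds when claiming effectiveness.

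**Conclusion.** The concern holds in limited form. Three things are certain from the text: 8 of the 16 items are preparatory; information search is among the named preparatory acts; and the FIS outcome called knowledge is made up only of preparatory acts, so it does not measure knowledge. It is also stated that the website's FIS and gear content goes to one group only.

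That a yes on an information-seeking item may reflect exposure follows from these facts, but its size cannot be fixed from the article. It depends on unseen item wording, on uptake and on the control rate. Under the stated assumptions, 14% to 33% of the intervention group would be enough to produce 10 points on a single item. The eight structural measures, and with them the whole strength-exercise topic, are not open to this route.

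The text does not support saying that half of the main outcome merely records delivery of the intervention, or that the trial as a whole can show nothing else.

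**What to change.** 1. Report the FIS topic as *FIS-rule preparatory acts*, and draw no conclusion about knowledge from it.
2. In every topic, analyze and report structural measures separately from preparatory acts.
3. Do not base a claim of changed injury preventive behavior on information-seeking items alone.
4. State whether using Wintersportklaar counts toward the information-seeking items. Use the intervention-use answers collected at one and three months (Procedures) to help interpret those items in the intervention group.

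The items are already classified and the use data are already being collected, so the cost is slightly more reporting and a narrower claim for the FIS topic and the preparatory items. The Results section says that enrolment is complete and analysis under way. Rewording the questionnaires is therefore probably no longer possible, and moving half of the declared items out of the main outcome would be a late change in a registered trial. Neither is needed.
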